# Effectiveness of a Patient-Centered Assessment With a Solution-Focused Approach (DIALOG-A) in the Routine Care of Colombian Adolescents With Depression and Anxiety: Protocol for a Multicenter Cluster Randomized Controlled Trial

**DOI:** 10.2196/43401

**Published:** 2023-02-08

**Keywords:** randomised controlled trial, adolescent, mental health, depression, anxiety, telemedicine, primary health care, Colombia

## Abstract

**Background:**

Colombia is a middle-income country in South America, which has historically had high rates of mental health problems, coupled with a scarcity of mental health care. There is growing concern for the mental health of the adolescent population within this region. There is a significant treatment gap for young people, especially those living in the most vulnerable areas. DIALOG+ is a low-cost patient-centered intervention that can potentially improve the delivery of care and quality of life for adolescents with mental health problems.

**Objective:**

This exploratory randomized controlled trial aims to evaluate the effectiveness, acceptability, and feasibility of an adapted version of the DIALOG+ intervention (DIALOG-A) in the community treatment of Colombian adolescents with depression and anxiety.

**Methods:**

In total, 18 clinicians and 108 adolescents will be recruited from primary health care services in Bogota and Duitama, Colombia. Clinicians will be randomized 2:1 to either the intervention (12 clinicians:72 adolescents) or control group (6 clinicians:36 adolescents). In the intervention arm, clinicians will use DIALOG-A with adolescents once per month over 6 months. The control arm will continue to receive routine care. Outcomes will be measured at baseline, 6 months, and 9 months following randomization. Semistructured interviews with all clinicians and a subset of adolescents in the intervention arm will be conducted at the end of the intervention period. Quantitative and qualitative analysis of the data will be conducted.

**Results:**

Trial recruitment was completed toward the end of October 2022, and follow-up is anticipated to last through to October 2023.

**Conclusions:**

This is the first study to test an adapted resource-orientated intervention (DIALOG-A) in the treatment of adolescents with depression and anxiety attending primary care services. If the results are positive, DIALOG-A can be implemented in the routine care of adolescents with these mental health problems and provide valuable insight to other middle-income countries.

**Trial Registration:**

ISRCTN Registry ISRCTN13980767; https://www.isrctn.com/ISRCTN13980767?q=ISRCTN13980767

**International Registered Report Identifier (IRRID):**

DERR1-10.2196/43401

## Introduction

### Background

Currently, an estimated 5.2 million adolescents are living in Colombia. During adolescence, physical, emotional, and social changes make individuals more vulnerable to mental health problems. Worldwide, and in Columbia, adolescence also marks the beginning of relationships and the emergence of sexuality, with a mature body capable of exercising it [1,2]. All these circumstances are intensified when adolescents live in an area with a history of conflict, displacement, inequality, poverty, violence, and lack of opportunities.

The internal conflict and violence experienced in Colombia for more than 50 years has led to the forcible displacement of 8.2 million individuals since 1985 [3], and a high proportion of the population is living in extreme poverty, which is currently estimated to be 12.2% (per the National Administrative Department of Statistics) [4]. This has contributed to fragile neighborhoods, particularly within urbanized inner-city areas, and deprived rural communities [3,4]. This complex picture has led to an increase in mental health illness among adolescents, including a rise in the prevalence of depression and anxiety, with a 1-year estimate of 4%-5% [5,6].

In Colombia, anxiety disorders are the most frequent, with an estimated prevalence of 15%-20%, and with rates reported to be as high as 31.9% among individuals aged between 13 and 18 years [7]. Similarly, rates of anxiety and depression are also commonly high among people aged 12 to 17 years. Using the Self-Reporting Questionnaire to assess this population, 13% of adolescents screened positive for depression [8,9].

Despite the high prevalence rates and long-term impacts of depression and anxiety, only half of the adolescents diagnosed with anxiety and depression in low- and middle-income countries (LMICs) access treatment, with a smaller percentage (20.5%) receiving at least the minimum standard of care. Consequently, less than 12% of adolescents in LMICs such as Colombia receive even minimally adequate treatment, pointing to an issue of both access and quality [10,11]. In Colombia, one of the most relevant barriers to mental health services delivery is a lack of sufficiently trained professionals [12,13]. Where resources are available, they tend to be distributed unevenly, concentrated in large cities, and fail to reach low-income or rural areas. Hence, low-cost, generic interventions that can be delivered by a range of staff (including those beyond the mental health system) are urgently needed to tackle depression and anxiety and ultimately improve adolescent health [14-16].

DIALOG+ is a technology-assisted and resource-orientated intervention based on quality-of-life research, patient-centered communication, and solution-focused therapy. Within DIALOG+, patients use a tablet to rate their satisfaction with 8 life domains (*mental health*, *physical health*, *job situation*, *accommodation*, *leisure activities*, *friendships*, *relationship with family/partner*, and *personal safety*) and 3 treatment aspects (*medication*, *practical help*, and *meetings with professionals*). This is followed by a 4-step solution-focused approach to identify and harness the existing resources available to the patient to address these concerns and improve their quality of life. This tool was established as an effective intervention for adults with mental health problems following a sustained program of research including multiple clinical trials [17-19].

Within a cluster randomized controlled trial (RCT) conducted across 6 European countries, regular use of the initial form of DIALOG+ over a year led to a better quality of life, fewer unmet needs, and higher treatment satisfaction for patients with psychosis. Following further modifications, DIALOG+, delivered once per month over 6 months, was compared to an active control in a pragmatic RCT involving 49 clinicians and 178 patients diagnosed with psychosis. Patients in the experimental group had a significant improvement in quality of life and lower general psychopathological symptoms after 3, 6, and 12 months. They also had fewer unmet needs and a better objective social situation. The effect size for improvements in quality of life ranged from 0.30 (95% CI 0.02-0.58) at 3 months to 0.32 (95% CI 0.06-0.58) at 12 months. Furthermore, DIALOG+ saved the National Health Service £1345 (US $1610.16) per patient, mainly due to fewer inpatient days required by the experimental group [17-19]. However, research has not assessed whether the intervention may also be effective for adolescents with common mental disorders.

### Study Aims and Objectives

This planned exploratory cluster RCT sits within the context of a larger research program called “Building resilience in adolescence - improving quality of life for adolescents with mental health problems in Colombia (BRiCs).” This is a collaborative project between Queen Mary University of London (London, the United Kingdom) and the Pontificia Universidad Javeriana of Bogota (Bogota, Colombia), which aims to improve health outcomes and quality of life for the adolescent population with depression and anxiety in Colombia. During the initial phase of the project, semistructured interviews and focus groups were conducted alongside a pilot study to adapt the existing intervention (DIALOG+) for use with adolescents [20]. The new intervention is called DIALOG-A.

Given this background, the overall aim of this study is to evaluate the effectiveness of DIALOG-A in the community treatment of adolescents with anxiety and depression in Colombia.

## Methods

### Study Design and Setting

A multisite, exploratory cluster RCT will be conducted to assess the effectiveness, acceptability, and feasibility of DIALOG-A for adolescents with anxiety or depression. In total, 18 clinicians and 108 adolescents will be recruited from primary health care services in Colombia and outcomes measured at baseline, 6 months, and 9 months following randomization.

The 3 sites included in this RCT in are based in 2 cities: Bogota and Duitama. Bogota is the capital city of Colombia, with 7.9 million inhabitants. Duitama, in contrast, is a small city of approximately 128,400 inhabitants in a rural location. Community mental health care is provided by primary health centers, which include an adolescent-friendly service. The population within Duitama is traditionally rural where poverty, alcohol intake, adult illiteracy, and family violence are common. Almost all the adolescents that use health services on this site belong to low socioeconomic status [21,22].

### Participants

#### Inclusion Criteria

The inclusion criteria for clinicians will be as follows: (1) being aged 18 years or older, (2) having a medical qualification as a general practitioner or pediatrician, (3) having regular contact with adolescent patients with anxiety and depression, (4) having at least 3 months of experience in working with adolescents, and (5) having no plans to leave their current position within the next 6 months.

The inclusion criteria for adolescents will be as follows: (1) being aged 13 to 16 years; (2) currently experiencing anxiety and depression, which is defined as a cutoff score of ≥7 on the Self-Reporting Questionnaire [23]; and (3) having the capacity to provide informed assent.

#### Exclusion Criteria

The exclusion criteria for adolescents will be as follows: (1) having severe mental illness (psychosis, bipolar disorder, or schizophrenia), (2) having cognitive impairment or severe learning disability, and (3) being unable to speak and understand Spanish.

#### Recruitment and Informed Consent

Each study site will include a coordinator who will recruit the clinicians for the study. A research assistant will recruit the adolescents, guide all participants through the informed consent process, and assess the outcomes at 3 defined time points (baseline, 6 months, and 9 months post randomization). A wider administrative staff member will schedule the follow-ups and provide the clinicians’ caseload to the research assistant to identify potential adolescent participants.

#### Clinicians

Each clinical site was identified from the national network of public and private primary care centers that provide care to the adolescent population of Colombia. An in-person meeting was arranged between the potential clinicians and study coordinators of each study site.

Eligible clinicians will provide their informed consent by signing and dating an electronic informed consent form via the Research Electronic Data Capture (REDCap) data management platform.

#### Adolescents

With the support of the administrative staff, research assistants will check each physician’s caseload to identify adolescent patients who meet the inclusion criteria. Potentially eligible adolescents will be then invited to a one-on-one meeting with the local site’s research assistant to discuss the study in more detail and answer any questions. This meeting will also be used to verify whether the inclusion criteria are met and to obtain informed assent and consent from the adolescents and their parents or guardians, respectively. During the study period, new referrals to the clinics will be screened for eligibility, and potentially eligible adolescents will be contacted by a research assistant.

Both the research team and the participants will keep a copy of the signed informed consent or assent form via REDCap. The researcher’s contact details will be provided on the informed consent form to allow participants to raise any questions or concerns they may have throughout the study. This process will take place before any data collection begins.

### Intervention

The enrolled clinicians will be contacted and invited to a web-based meeting on a free videoconferencing platform such as Zoom or Microsoft Teams with a researcher who will re-explain the objectives of the RCT and answer any questions or concerns that are raised.

Clinicians randomized to the intervention arm will use DIALOG-A with the adolescents once per month for 6 months. Clinicians allocated in this arm will receive a tablet, with the DIALOG-A app already preloaded. Each DIALOG-A session will last approximately 20 minutes and will take place face to face with the clinician. Where it is not possible for a face-to-face consultation to occur, a web-based consultation will be conducted in line with standard care procedures within the health care service. In each session, the clinician will ask the patient to rate all the domains on the DIALOG scale, which will then be followed by the 4-step solution-focused approach. After completing the 6-month intervention with the DIALOG-A app, clinicians and adolescents can continue using the intervention depending on their needs, and this will be documented and considered in the analysis.

### Treatment-as-Usual Control

The intervention group will be compared to treatment-as-usual control. Clinicians in the control arm will follow the routine care provided for adolescents accessing primary care services. The frequency of the consultations during the duration of the RCT will vary depending on the clinical criteria of the respective clinician and the adolescent; however, this will be, on average, once per month.

### Training and Supervision

All clinicians in the intervention arm will receive training in DIALOG-A through one-to-one web-based sessions with a researcher, which will take between 45 and 60 minutes. During these training sessions, clinicians are provided with reading material, instructions, and examples on how to use the DIALOG-A app with adolescents [24]. Clinicians can contact any member of the local research team for further sessions and for advice or support at any time of the RCT. Refresher training will be provided to clinicians in the intervention arm depending on their needs, with a minimum of 2 refresher sessions provided throughout the RCT.

All clinicians allocated to either the intervention or control arms will receive training in the diagnosis and treatment of adolescent depression and anxiety through an asynchronous web-based course. These training sessions include academic passages on anxiety disorders, mental health disorders related to trauma and stress, and mood disorders, which are developed by adolescent mental health specialists from Pontificia Universidad Javeriana. Clinical cases and discussion forums will be available as well. A final quiz with a minimum passing score of 80% must be completed by participating clinicians.

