### Randomization

To reduce the potential for contamination, the unit for randomization will be the clinician. Clinicians will be randomized 2:1 to either the intervention (12 clinicians:72 adolescents; to have DIALOG-A sessions once per month for 6 months) or to the treatment-as-usual control group (6 clinicians:36 adolescents; appointments scheduled as and when needed, without DIALOG-A or specific assessments). For existing patients, who are already on the caseload, adolescent participants will be recruited and baseline assessments conducted prior to their clinician being randomized. Individuals who are new to the service and are not on the existing caseload of a clinician will be randomly assigned to either the intervention or control arm and then to an appropriate clinician, following completion of the baseline measures. We will record the number of adolescent participants who are recruited and individually randomized.

Clinicians and adolescents will not be blinded to allocation due to the nature of the intervention. However, to reduce bias, randomization will be carried out by a blinded independent statistician at the Unit for Social and Community Psychiatry, Wolfson Institute of Population Health, Queen Mary University of London. Baseline data collection will occur before randomization, and all research assistants involved in outcome data collection will be blinded to allocation. We will additionally record the number of postrandomization recruits; for example, individuals who were recruited after their clinician has been randomized.

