### Quantitative Data

All participants (clinicians and adolescents) will be asked to complete a sociodemographic questionnaire at baseline. Clinicians will be asked to rate the Clinical Global Impression questionnaire after every appointment.

The primary outcomes will be collected at 6 months, with a further follow up of 9 months post randomization—these include symptoms of depression measured using the 8-item Patient Health Questionnaire [25] and symptoms of anxiety measured using the 7-item Generalized Anxiety Disorder scale [26].

All secondary outcomes will be collected at baseline, 6 months, and 9 months (unless otherwise stated)—these include quality of life measured using the Manchester Short Assessment of Quality of Life [27], mental health symptom levels measured using YP-CORE [28], social support measured using the Multidimensional Scale of Perceived Social Support [29], empowerment measured using the Youth Efficacy/Empowerment scale [30], self-esteem measured using the Rosenberg Self-Esteem Scale [31], and economic outcomes measured using a modified Client Service Receipt Inventory [32].

In addition to the outcome data described above, we will collect process measures, including the number of DIALOG-A interventions performed, the date and duration of those sessions, the scores obtained on the DIALOG scale within each session, key topics discussed during the 4-step approach, and what actions were agreed upon. The DIALOG-A app on the tablet is able to capture the data required. This information will be synchronized to a server that the research team can access.

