### Statistical Analysis

The analysis of data will be discussed and agreed upon with the local and international research teams, with a statistical analysis plan developed by the statistician and signed off by trial steering committee. The local research team will take a leading role in the management and analysis of the data. Data analysis will not be conducted prior to signing off and blinding of the members of the research team, including the statistician responsible for the analysis, who will remain blinded throughout.

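### The statistician cannot stay blinded for the whole analysis under the 2:1 design, and the blinding of outcome assessors is promised but left unprotected by the support and data-access rules

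*Protocol article*

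**What the plan says.** The protocol article makes two blinding promises.

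- **Assessors** (Randomization): "all research assistants involved in outcome data collection will be blinded to allocation".
- **Analyst** (Statistical Analysis): the research team is to be blinded, "including the statistician responsible for the analysis, who will remain blinded throughout".

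Four other rules bear on them.

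- **Clinician support** (Training and Supervision): "Clinicians can contact any member of the local research team for further sessions and for advice or support at any time of the RCT". This stands in the paragraph on training the intervention-arm clinicians in DIALOG-A.
- **Session data** (Quantitative Data): the app records the number, dates, duration, ratings and content of sessions, and "This information will be synchronized to a server that the research team can access".
- **Who assesses** (Recruitment and Informed Consent): "A research assistant will recruit the adolescents, guide all participants through the informed consent process, and assess the outcomes at 3 defined time points". The Adolescents subsection places this research assistant at the local site.
- **Who analyses** (Statistical Analysis): "The local research team will take a leading role in the management and analysis of the data".

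The Intervention section brings DIALOG-A use after month 6 into the analysis, and Quantitative Data Analysis does the same for the number of sessions received. Strengths and Limitations names only adolescents and clinicians as unblinded.

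**The concern.** A promise of blinding is only as good as the rules on who speaks to whom and who sees which data. Here those rules are stated, and they are broader than the promises allow.

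Only intervention clinicians have a reason to ask for more DIALOG-A training. A support request to the research assistant therefore discloses that clinician's arm, and with it the arm of the adolescents under that clinician. A look at the app server does the same. The statistician needs neither route: the arm sizes and the one-arm session data are in the analysis itself.

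The primary outcomes are symptom scores for depression and anxiety, collected by a research assistant from adolescents who know their arm. Blinding of assessor and analyst is one of several safeguards. The protocol also has randomization by an independent statistician, baseline assessment before randomization, and an analysis plan signed off before analysis. If the procedures are followed as written, the trial report could claim blinding that was not secured for assessors and not attainable for the analyst. That claim would carry into the full trial which this exploratory study is meant to inform.

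**Working it through.** **1. The planned arm sizes.** Inputs from Study Design and Setting and Randomization: 18 clinicians, 108 adolescents, ratio 2:1.

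- Clinicians: 18 × 2/3 = 12 and 18 × 1/3 = 6.
- Adolescents: 108 × 2/3 = 72 and 108 × 1/3 = 36.
- Per clinician: 108 / 18 = 6, the same in both arms (72/12 and 36/6).

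These reproduce the protocol's figures: "Clinicians will be randomized 2:1 to either the intervention (12 clinicians:72 adolescents; to have DIALOG-A sessions once per month for 6 months" and "treatment-as-usual control group (6 clinicians:36 adolescents; appointments scheduled as and when needed, without DIALOG-A or specific assessments". Taking the two cities as strata (12 clinicians in Bogota, 6 in Duitama, from Proposed Sample Size), the split is 8:4 and 4:2, so the same cue appears within each.

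**2. Does the size cue survive dropout?** The protocol gives no expected retention, so the rates below are assumptions, and individuals are treated as independent. Let I be the number retained in the intervention arm, binomial with n = 72 and rate r_I. Let C be the number retained in the control arm, binomial with n = 36 and rate r_C. Someone who takes the larger coded group to be the intervention is not correctly guided when I ≤ C:

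P(I ≤ C) = Σ over c from 0 to 36 of P(C = c) × P(I ≤ c)

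| r_I | r_C | Expected I vs C | P(I ≤ C) |
|---|---|---|---|
| 90% | 90% | 64.8 vs 32.4 | below 0.00001 |
| 80% | 80% | 57.6 vs 28.8 | below 0.00001 |
| 70% | 70% | 50.4 vs 25.2 | below 0.00001 |
| 60% | 60% | 43.2 vs 21.6 | 0.00002 |
| 70% | 90% | 50.4 vs 32.4 | 0.00003 |
| 60% | 90% | 43.2 vs 32.4 | 0.011 |
| 50% | 90% | 36.0 vs 32.4 | 0.25 |
| 50% | 100% | 36.0 vs 36.0 | 0.55 |

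The cue becomes unreliable only when about half the intervention arm is lost while the control arm is nearly complete. Dropout that clusters by clinician would widen the spread somewhat. Even then, the 12 vs 6 clinician clusters needed for a model that accounts for clustering give the same information.

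**3. A second cue that does not depend on size.** Session counts and continued DIALOG-A use exist in one arm only. Whoever merges or analyses them with the participant data can see which group has them.

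**4. Assessors: the rules side by side.** No arithmetic applies.

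- Randomization: every research assistant who collects outcomes is blinded.
- Recruitment and Informed Consent, with Adolescents: that person is the local site's research assistant and sees participants at all three time points.
- Training and Supervision: clinicians may turn to anyone on the local team. No role is excepted.
- Quantitative Data: the research team can reach the session data. No role is excepted.

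The first rule can be kept only if the last two are narrower in practice than they are on paper. With 6 adolescents per clinician, one support request that reaches the research assistant would disclose the arm of about six participants.

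**The case against.** The strongest reply concerns the assessors. The Randomization section states a specific rule, while the support sentence is a general permission: clinicians may make contact, and nobody is required to answer. Initial training is given by a researcher, not by a research assistant. Coordinator, research assistant and administrative staff are described as separate roles. Delegation lists and server permissions usually sit in a full protocol, not in a journal article.

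Much of this stands, and it rules out several stronger readings that a reader might infer.

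- **That assessor blinding is impossible.** The documents show an open route, not a certain breach.
- **That the 2:1 ratio unblinds assessors.** Arm size tells a research assistant nothing about a given participant's allocation.
- **That the local team's lead in analysis means the trainers are the analysts.** Blinding attaches to persons, and the article does not say that the same people do both.
- **That knowing an adolescent's clinician reveals the arm.** It does so only once the clinician's allocation is known. For existing patients, recruitment and baseline assessment precede the clinician's randomization.
- **That the probability of unblinding can be calculated from adolescents' own disclosures at visits.** The documents give no disclosure rate, and that risk is common to any open-label trial with blinded assessors. It would not measure the effect of the support and server rules.

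Also, if adolescents complete the two symptom scales themselves (the article does not say), a blinded assessor protects less in any case. And a signed analysis plan limits the harm that an unblinded statistician could do.

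What the reply does not remove is the wording. The point is not that detail is missing: the article states affirmatively that any local team member may be contacted and that the research team can access the data. It also states that the statistician's blinding lasts throughout, which its own design prevents.

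**Conclusion.** The point holds in two parts of different strength.

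**Analyst.** Blinding for the entire analysis is not achievable as written. The 72:36 and 12:6 splits and the one-arm session data reveal allocation in any by-arm analysis. The size cue fails with probability of at most 0.00002 under equal retention of 60% to 90%, and about 0.011 at 60% against 90%. These figures rest on assumed retention, on independence between individuals, and on recruitment close to plan. The session-data cue needs none of these assumptions.

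**Assessors.** Blinding is possible but unprotected, and the passage that promises it is inconsistent with the rules on clinician support and server access. The documents do not support a probability of unblinding, a size or a direction of bias in the symptom scores.

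No sample size or power figure depends on this. It is a correction that should be made, not a threat to the exploratory trial as a whole.

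**What to change.** 1. **Training and Supervision.** Direct requests for further sessions, advice or support to designated trainers who collect no outcome data, in place of the whole local team.
2. **Quantitative Data.** State that research assistants who assess outcomes have no access to the app server until the 9-month assessments are complete.
3. **Follow-up forms.** Add an item at 6 and 9 months on which the research assistant records suspected unblinding, and report it by arm.
4. **Statistical Analysis.** Drop the claim that the statistician is blinded for the whole analysis. State instead that the analysis plan and code are finalised on data with a shuffled allocation variable and locked before true allocation and session data are merged. This guards against data-driven choices of analysis without claiming a property that the design cannot have.

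I would not impose self-completion of the two symptom scales at follow-up as a further safeguard. The article does not state the present mode, and a change could alter the measurement between baseline and 6 months.

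**Cost.** Protocol wording, server permissions and one form item. Support calls go to fewer people, a small loss of convenience. The article reports that recruitment ended toward the end of October 2022 and that follow-up runs through October 2023, so the changes can still be made during follow-up. Item 4 has to be in place before any by-arm analysis.
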